### Implementation strategies

Several strategies have been chosen in order to support the implementation of the VESPEERA programme. First, the CareCockpit software is used, providing a platform to GP-practices that assists with organising patient information, organising care planning, guidance through assessments and automatic generation of documents. The CareCockpit is routinely used in Baden-Wurttemberg within the practice-based case management programme PraCMan (*Hausarztpraxis-basiertes Case Management*)) and is now enhanced by an additional module for the VESPEERA programme [15]. GP-practices receive the CareCockpit-software free of charge. Second, representatives of all stakeholders, thus clinicians, GPs, patients, sickness funds and researchers, have been involved in the development of assessment instruments and study documents in order to increase acceptance and utilisation. In several workshops the intervention components and all their items were discussed with regard to its relevance, information value, feasibility, and degree of sensitivity as well as wording. Third, GPs and VERAHs will participate in a workshop to be instructed in software utilisation and study processes. The workshops are delivered in a train-the-trainer format, i.e. the study team trains a certain number of GPs who then lead regional workshops for their participating colleagues. Fourth, participating hospitals will hand in a description of their individual implementation plan. In order to facilitate the integration of study components into clinical processes, different approaches are suitable for different hospitals. Therefore, each hospital will provide information on how they will ensure the identification of study patients, the use of the admission letter, the execution of the telephonic discharge conversation, the dissemination of the patient discharge information, and the determination of the HOSPITAL Score. Hospitals can choose to either integrate the intervention components into their medical information system or to choose a paper-based solution, depending on their processes. Additionally, hospitals are offered two options to provide the patient discharge information: (a) hospitals use the template provided by the study team or (b) hospitals integrate the elements of the study template into their own documents. Fifth, all stakeholders will receive feedback reports in form of benchmarking reports in September 2018, June 2019 and December 2019. The feedback reports are based on claims data, data from the CareCockpit and patient survey data, aggregated on a hospital / GP-practice level. The feedback reports will be discussed in moderated interdisciplinary feedback meetings. GPs, representatives of the hospitals as well as patients will participate in these meetings and discuss options for potential improvement. Additionally, hospitals and GP-practices will receive expense allowances for conducting patient-related care services as well as lump sums for study organisation and participation in workshops and feedback meetings.

### Data sources

Data sources for the evaluation are claims-based data from AOK Baden-Wurttemberg, data from the CareCockpit software, primary data in the form of patient surveys in the intervention group as well as a control group, and data collected in participating hospitals in order to determine the HOSPITAL Score. This includes haemoglobin and sodium levels, length of stay, type of admission (elective vs. non-elective), discharge from an oncology service or execution of an oncological treatment, any OPS-coded procedure and number of hospital stays in the last 12 months.

CareCockpit data includes the pseudonym generated for data linkage, diagnoses, the medical question for admission, information on previous antibiotic prescriptions, living situation, long-term care related items (such as ADL and IADL-scale), medical information (such as pain, wounds, alarming symptoms for medical emergencies, PHQ-2 instrument), compliance to medicinal therapy, the items of the HOSPITAL Score as well as process data (provision of information to patients, information on whether any follow-up care has been initiated and successfully executed).

The patient survey questionnaire includes the following instruments: sociodemographic questions, the validated EQ-5D for health related quality of life [8] as well as selected items from the validated PEACS-instrument for satisfaction with cross-sectoral care concerning the admission and discharge process [16]. Patient surveys are conducted in GP-practices belonging to the intervention group as well as GP-practices that build a control group with all patients who, in the first (t0) and in the last 3 months of the intervention phase (t1) respectively come into their GP-practice after a hospital stay. The intervention phases can vary between the GP-practices of the intervention group depending on when the respective practice actually started its participation in VESPEERA.

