## Methods/design

An open prospective quasi-experimental trial will be conducted in multiple centres. Development of study material has started in October 2017. Recruitment of patients and implementation of study components (intervention phase) has started in May 2018 and will last through September 2019, comprising a total of 17 months. Participants can be enrolled until September 2019. All evaluations and publications are planned to be completed by the end of September 2020. Figure 1 illustrates the study timeline.

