### Outcomes

The primary outcome is the number of rehospitalisations due to the same indication (three-digit ICD-10-GM code) within a time frame of 3 months (90 days) to the outpatient sector. This outcome is collected from claims-data on a case level, meaning that each patient can have more than one rehospitalisation, whereof all are considered in the analyses.

The following indicators have been defined as secondary outcomes and are based on pseudonymised claims-data, data collected within the CareCockpit software in GP-practices as well as patient survey data:number of rehospitalisations due to the same indication (three-digit ICD-10-GM code) within a time frame of 30 daysnumber of hospitalisations due to ambulatory care-sensitive conditions [17]number of patients discharged to the outpatient sector from a participating hospital where the prescription of medication is delayed [18]number of patients discharged to the outpatient sector from a participating hospital where referral to other health practitioner/s (*Heilmittel*) is delayednumber of patients discharged to the outpatient sector from a participating hospital where prescription for medical products/devices (*Hilfsmittel*) is delayednumber of patients discharged from a participating hospital who use emergency or rescue services (emergency medical service (*Ärztlicher Bereitschaftsdienst*), emergency ambulance (Notarztwagen), ambulance emergency response vehicle (*Notarzteinsatzfahrzeug*), ambulance, rescue helicopter (*Primärtransport – Luft*) within a time frame of 3 monthsaverage care cost per year and patient participating in the VESPEERA programmepatient-reported experiences and health-related outcome of cross-sectoral care using the German version of the instrument Patients’ Experiences Across Health Care Sectors (PEACS) [16]health-related quality of life, using the instrument EuroQol (EQ-5D) [19].

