### Recruitment

All eligible GP-practices located within the predefined districts will be contacted by the HÄVG (*Hausärztliche Vertragsgemeinschaft,* HÄVG, the organisation that manages the GP-centred care contracts for the German Association of General Practitioners) via fax or on other communication channels such as newsletters and in continuing education workshops. If interested in participation, GPs and VERAHs sign up for the training described above. During the training they will receive detailed information about the study and sign the informed consent form.

Participating practices as study sites will check the inclusion criteria for a) patients with a planned hospital admission and b) patients after discharge after an unplanned hospital stay, provide the study information, and receive the signed informed consent forms which remain at the study site.

For the recruitment of the control group for the patient survey, GP-practices outside the intervention region will check the inclusion criteria for patients after hospital discharge. They hand out the patient survey questionnaire to eligible patients. Patients give their consent by filling in the anonymous questionnaire. Controls for the patient survey are recruited by GP-practices outside the intervention region.

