### Data collection and management

Primary and secondary outcomes, as well as patient characteristics, are extracted from claims-data at the health insurer involved, CareCockpit data and primary data from a patient survey.

Claims-based data are collected for a time frame starting 6 months before baseline until 3 months after the intervention phase. Data from the CareCockpit is transferred along with administrative data each quarter year.

For the conduction of the patient survey, GP-practices are informed in advance on when to conduct the survey and they receive all material needed including the patient questionnaires, the sealed box to collect them, and detailed information on how to conduct the survey in the practice. The patients are asked in the practice by their physician after discharge to take part in the survey by filling in the questionnaire in the practice. Questionnaires will be handed out to all eligible patients per practice and time point in both intervention and control practices. The sealed boxes with filled-in questionnaires will be sent by mail using an enclosed post-paid box directly to the aQua-Institute.

The hospitals have the choice to either integrate the questionnaire into their hospital information system as an electronic questionnaire (transfer to the aQua-Institute via secure file transfer protocol (SFTP)-servers) or to fill in paper-based questionnaires that are sent to the aQua-Institute via mail using enclosed post-paid envelopes. If GP-practices are responsible for determining the HOSPITAL Score, the items of the HOSPITAL Score are part of the assessment for planning of follow-up care within the CareCockpit and will be transferred to the evaluating institutions along with other CareCockpit data. All data necessary to determine the score can be extracted from the discharge letter.

As the intervention is implemented in a pragmatic study design, differences in quality between the GP-practices and hospitals can occur. For quality assurance purposes, all GP-practices are therefore continuously being contacted via telephone by the study central office. Within the phone calls, recruitment status in the GP-practice is being checked and support with the implementation is offered. Additionally, any issues that occur with the implementation will be addressed in feedback meetings. Furthermore, the CareCockpit software guides through the assessments.

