#### Primary analysis

In the primary analysis, a difference-in-difference model is applied [21, 25, 26]. The change of the primary outcome (before vs. after the intervention) of each intervention group will be pairwise compared to the control group. Put in a simple way, the following model will be estimated:$$ {\mathrm{rehospitalisation}}_{\mathrm{t},\mathrm{i}}={\upbeta}_0+{\upbeta}_{\mathrm{T}}\mathrm{x}\ {\mathrm{t}\mathrm{ime}}_{\mathrm{t},\mathrm{i}}+\kern0.37em {\upbeta}_{\mathrm{I}}\mathrm{x}\ {\mathrm{i}\mathrm{ntervention}}_{\mathrm{i}}+\kern0.37em {\upbeta}_{\mathrm{I}\mathrm{x}\mathrm{T}}\mathrm{x}\ {\left(\mathrm{intervention}:\mathrm{time}\right)}_{\mathrm{t},\mathrm{i}}. $$

The index t describes the point in time, i is the index for the considered observation. The following parameters will be estimated:β_0_: interceptβ_T_: effect of time; the general change from before to after the interventionβ_I_: difference between groups at baselineβ_IxT_: difference between the change (before and after comparison) in the control and in the intervention group; the main parameter for the outcome evaluation

The assumptions of this model are sufficiently discussed in the literature. The parameter β_IxT_ is the main parameter to evaluate the effectiveness of the intervention, describing the difference in changes between the two groups over time.

The above model is adjusted for the covariate service level of the hospital and the location (general allocation to districts). Other covariates will be already considered during the matching procedure when generating the control group.

The primary outcome is binary. Thus, logistic regression models will be applied. Furthermore, there is a hierarchical structure underlying the data, with cases nested in patients, and patients nested in practices or hospitals, respectively. This structure is considered in the model by including random intercepts at each level. The combination of random and fixed effects results in a mixed logistic regression model. A compound symmetry correlation structure will be assumed when fitting the models.

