#### Secondary analysis and sensitivity analysis

In addition to the primary analysis, further analyses will be conducted. First, again using the primary outcome but including 12 time points (six before the intervention and six after the intervention (measured month-wise), time trends before and after the intervention will be compared using interrupted time-series-models [27, 28]. Secondary endpoints will be analyzed using the same strategy as used in the primary analysis with adjustments of the models as necessary.

Furthermore, descriptive statistics of all collected data will be performed. Continuous variables will be described using means, standard deviations, median, minimum, maximum, and first and third quartile, separately for each intervention group and the control groups as well as for the total population. Categorical variables will be reported using absolute and relative frequencies.

As claims-based data are used, no missing values are expected to occur, therefore no imputation procedures need to be carried out.

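### The patient survey has no unexposed wave, so a t0-to-t1 difference-in-difference on PEACS and EQ-5D understates the programme effect by an unknown amount

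*Protocol article*

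**What the plan says.** The Data sources section of the protocol article describes a survey in intervention and control practices of patients who attend after a hospital stay, "in the first (t0) and in the last 3 months of the intervention phase (t1) respectively". It lets the phase differ between intervention practices, "depending on when the respective practice actually started its participation in VESPEERA". Methods/design gives the phase a length of 17 months and says what it is: "Recruitment of patients and implementation of study components (intervention phase) has started in May 2018 and will last through September 2019, comprising a total of".

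Under Outcomes, PEACS and EQ-5D are the last two of nine secondary outcomes. Under Secondary analysis and sensitivity analysis: "Secondary endpoints will be analyzed using the same strategy as used in the primary analysis with adjustments of the models as necessary". The strategy referred to is in Primary analysis: "The change of the primary outcome (before vs. after the intervention) of each intervention group will be pairwise compared to the control group". There the group-by-time interaction is named as the main parameter for effectiveness, and the group term as the difference between groups at baseline.

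The only period before the programme is in Data collection and management: "Claims-based data are collected for a time frame starting 6 months before baseline until 3 months after the intervention phase". Nothing comparable is given for the survey.

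**The concern.** A difference-in-difference needs a measurement taken before exposure. The claims outcomes have one and the survey does not. Because the phase is counted from each practice's own start, staggered entry does not help: t0 follows programme start in every intervention practice. Any benefit already present at t0 is taken into the group term as though it were a pre-existing difference, and is then subtracted from the interaction. If that interaction is read as the programme effect, a real benefit on patient experience or quality of life could be reported as smaller than it is, or as absent.

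**Working it through.** The Sample size calculation section covers rehospitalisation only. There is no stated effect size or power for PEACS or EQ-5D to reproduce, so the check is algebraic, with assumed uptake.

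**Expectation of the contrast.** Let D be the full programme effect on a survey mean, f0 and f1 the shares of it delivered at t0 and t1, and T the common time trend (parallel trends assumed).

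- Change in intervention practices: T + f1 × D − f0 × D
- Change in control practices: T
- Difference-in-difference: (f1 − f0) × D
- Group term: true pre-existing difference + f0 × D

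With an unexposed t0 (f0 = 0) the contrast would return the whole t1 effect, f1 × D. As described, it returns the fraction (f1 − f0)/f1 of it.

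**Size under assumed uptake.** The article gives neither f0 nor f1. Assume delivery rises linearly from 0 to full over r months after practice start, within a 17-month phase. t0 is months 0 to 3 and t1 is months 14 to 17. For r of 3 or more, f0 = 1.5/r. For r = 1, f0 = (0.5 + 2)/3 = 0.833. For r = 17, f1 = 15.5/17 = 0.912; for the shorter ramps f1 = 1.

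| Ramp r (months) | f0 | f1 | Contrast as share of D | Contrast as share of t1 effect |
|---|---|---|---|---|
| 0 (full from day 1) | 1.000 | 1.000 | 0.000 | 0% |
| 1 | 0.833 | 1.000 | 0.167 | 17% |
| 3 | 0.500 | 1.000 | 0.500 | 50% |
| 6 | 0.250 | 1.000 | 0.750 | 75% |
| 12 | 0.125 | 1.000 | 0.875 | 88% |
| 17 | 0.088 | 0.912 | 0.824 | 90% |

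A practice that joins late has a shorter phase. With a 6-month phase and a 6-month ramp, f0 = 0.25 and f1 = 0.75, so 0.50/0.75 = 67% of the t1 effect remains.

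**Consequence for power.** As a reference only, take a survey contrast that would have 80% power at two-sided 5% with an unexposed t0. If a fraction k of the effect is retained, power = Φ(2.80k − 1.96) + Φ(−2.80k − 1.96), where 2.80 = 1.96 + 0.84.

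| k | Power |
|---|---|
| 1.00 | 80% |
| 0.90 | 71% |
| 0.75 | 56% |
| 0.50 | 29% |
| 0.25 | 11% |
| 0 | 5% |

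Restoring 80% power multiplies the sample size by 1/k²: 1/0.75² = 1.8-fold, 1/0.50² = 4-fold.

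**The case against.** A reader might infer that the survey analysis wipes out the effect altogether. The article does not support that. Complete cancellation needs delivery at t0 to equal delivery at t1, and several features point to partial exposure at t0:

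- Questionnaires go to all eligible patients, not only to programme recipients.
- Patients admitted before their practice started cannot have had the pre-admission assessment and letter, and such patients concentrate in t0.
- Feedback reports, moderated meetings and telephone support are spread over the study, so implementation may build up gradually.

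A reader might also infer that the authors present t0 as a baseline. They do not use that word for it; t0 takes that role only through the analysis strategy. Nor does anonymity add to the problem. The sentence "Patients give their consent by filling in the anonymous questionnaire" stands in the paragraph on recruiting survey controls, and a difference-in-difference on repeated cross-sections needs no individual linkage.

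The strongest defence is that secondary endpoints follow the primary strategy with model adjustments as needed, and that the survey model belongs in an analysis plan not at hand. Adjustment is indeed unavoidable, since a per-arm logistic model with claims-matched controls cannot be carried over unchanged to survey scales and a separate set of about 50 control practices. But the article fixes both the survey timing and the general strategy. Changing the model form does not create a pre-programme wave, and the clause names no other contrast.

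It also stands that the reach is limited. Two of nine secondary outcomes are affected, and when f0 lies between 0 and f1 the bias is toward no effect, so it does not manufacture a benefit.

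**Conclusion.** The point holds as attenuation of unknown size. Both survey waves lie inside each practice's intervention phase, so a before-versus-after difference-in-difference on PEACS and EQ-5D estimates (f1 − f0) × D, the change from early to late implementation. Under the assumed ramps of 3 to 17 months in a 17-month phase it keeps about 50% to 90% of the t1 effect. Under faster uptake it keeps less, down to none if delivery is full from the first day. These figures rest on parallel trends, a linear outcome scale and linear uptake; the article gives nothing with which to choose among them. The primary outcome and the other claims-based outcomes are outside this point.

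**What to change.** State in the analysis plan, before the survey data are analysed:

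1. The t0-to-t1 interaction for PEACS and EQ-5D is reported as change during implementation and is not interpreted as the programme effect.
2. The programme contrast for the survey is intervention versus control practices at t1, from a mixed model with a practice random intercept, adjusted for the sociodemographic items in the questionnaire. The report says that this contrast has no pre-intervention baseline and is open to confounding between regions.
3. If admission or discharge dates are available, add a sensitivity difference-in-difference in which t0 in intervention practices is restricted to hospital stays and survey visits not yet exposed to the programme. Discharge before practice start is not sufficient alone, because the follow-up assessment takes place in the practice after discharge.

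Pooled t0 and t1 should not be the main contrast. With equal waves it recovers (f0 + f1)/2 of D, for example (0.5 + 1)/2 = 75% with a 3-month ramp, against 100% at t1.

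The cost is wording, plus one sensitivity analysis if dates exist. The price in interpretation is real: the t1 contrast exchanges a bias toward no effect for possible regional confounding of unknown direction, which sociodemographic adjustment may not remove. Reporting both contrasts, each under its proper name, lets the reader see this.

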### Outcomes

The primary outcome is the number of rehospitalisations due to the same indication (three-digit ICD-10-GM code) within a time frame of 3 months (90 days) to the outpatient sector. This outcome is collected from claims-data on a case level, meaning that each patient can have more than one rehospitalisation, whereof all are considered in the analyses.

The following indicators have been defined as secondary outcomes and are based on pseudonymised claims-data, data collected within the CareCockpit software in GP-practices as well as patient survey data:number of rehospitalisations due to the same indication (three-digit ICD-10-GM code) within a time frame of 30 daysnumber of hospitalisations due to ambulatory care-sensitive conditions [17]number of patients discharged to the outpatient sector from a participating hospital where the prescription of medication is delayed [18]number of patients discharged to the outpatient sector from a participating hospital where referral to other health practitioner/s (*Heilmittel*) is delayednumber of patients discharged to the outpatient sector from a participating hospital where prescription for medical products/devices (*Hilfsmittel*) is delayednumber of patients discharged from a participating hospital who use emergency or rescue services (emergency medical service (*Ärztlicher Bereitschaftsdienst*), emergency ambulance (Notarztwagen), ambulance emergency response vehicle (*Notarzteinsatzfahrzeug*), ambulance, rescue helicopter (*Primärtransport – Luft*) within a time frame of 3 monthsaverage care cost per year and patient participating in the VESPEERA programmepatient-reported experiences and health-related outcome of cross-sectoral care using the German version of the instrument Patients’ Experiences Across Health Care Sectors (PEACS) [16]health-related quality of life, using the instrument EuroQol (EQ-5D) [19].

